### Population, inclusion and exclusion criteria

All elderly patients (65+ years of age, living in three municipalities (Herlev, Rødovre or Gladsaxe)), hospitalised for minimum two days at the wards of geriatric medicine of the University Hospital of Herlev, will be screened by a research assistant for nutritional risk. Patients will be excluded from the study when they; suffer from senile dementia or terminal disease; can not understand the Danish language; are residing in nursing homes; or are not able to or willing to give informed consent.

### Nutritional status

Patients are eligible for this study if they are identified at nutritional risk according to the following criteria in the level 1 screen NRS2002 [13]:

▪ Is Body Mass Index (BMI in kg/m^2^) < 20.5? and/or

▪ Has the patient lost weight within the last 3 months? and/or

▪ Has the patient had a reduced dietary intake in the last week? and/or

▪ Is the patient serious ill? (e.g. in intensive therapy)

▪ The nutritional risk will be confirmed by the research assistant by means of medical records.

### Intervention

#### Discharge follow-up in all patients' home by GPs

The follow-up consists of three contacts, conducted approximately one, three and eight weeks after discharge in both control and intervention patients. The contacts are guided by an agenda (based on [12]):

▪ Checking the discharge letter for specific recommended paraclinical or clinical follow-up

▪ Check need for adjustment of medication

▪ Check of the family's medical cabinet

▪ Checking the general health status (nutrition (vitamin D), physical activity, alcohol, continence, depression, dementia, and so on)

The contacts are either in the GPs clinic or as a home visit depending on the patients overall condition.

#### Patients randomised to nutritional intervention

The research registered dieticians ([name] and [name]) will perform a comprehensive nutritional assessment at the first home visit, as a basis for developing a nutrition care plan consistent with estimated nutritional requirements and nutritional rehabilitation goals. Basal metabolic rate will be assessed by means of Harris-Benedict and a factorial method, eventual accounting for weight gain factors, will be used to estimate the total energy- and protein requirement for each patient (based on [15]).

To assess dietary intake, the RDs will perform a standardised dietary interview with each participants to determine total energy and protein intake at each visits. Strategies for achieving energy and protein requirements will include dietary counselling with attention to nutritional risk factors, timing, size and frequency of meals, recommendations for nutrient dense foods and drinks, and provision of leaflets with information. Supplementation with energy and protein-dense meals-on-wheels, subscription of commercial oral nutritional supplements as well as vitamin D, calcium and other vitamin-minerals will also be considered to achieve optimal nutritional status.

All in all, the RDs will perform three home visits, to perform dietetic care and maximise participants' nutritional status by way of reviewing the nutrition care plan, dietary counselling, motivation and education, monitoring participant weight, and ensuring energy and protein requirements are achieved. If it is considered relevant the participants will receive short follow-up consultations by telephone by the RDs in order to give advice and to stimulate compliance to the proposed nutritional intake (in-between the home visits).

At least one counselling will be together with the patient's GP, in order to discuss the treatment, either in home or at the GPs clinic.

### Procedure

After obtaining patients informed consent (either at the hospital or right after discharge) an inventory will be made of possible confounders. This includes the following characteristics:

▪ Socio-demographic data (age, gender)

▪ Medical diagnosis

▪ New Mobility Score (assessment of mobility before admission (total score 0-9) [16]

▪ Additional discharge interventions (e.g. outgoing hospital teams, discharge follow-up phone calls etc.)

▪ Prescription/use of commercial oral nutritional supplements

▪ Prescription of Vitamin D supplements

▪ Prescription of rehabilitation in the form of physiotherapy

After 12 weeks participants will be contacted via telephone and mail to organise the follow-up assessment.

If there is no response then the research assistants will contact the hospital to check for an eventual re-admission.

### Outcome parameters

Outcome parameters will be measured in the participants' home as soon as possible after discharge (t = 0) and at +12 weeks (t = 12).

Primary outcome is prevalence of re-admissions. All outcome parameters that will be measured are listed below. If nothing else is stated the data is gathered by the research assistants.

#### Re-admissions (t = 12)

A register-based evaluation of readmissions will be done after 12 weeks. Data on admission to the hospital will be based on the National Patient Register. Information about the number of days to first re-admission and the number of days spent in hospital will also be collected from the Register.

#### Nutritional status (weight, height, BMI) (t = 0 and t = 12)

Weight is measured (with patients wearing light indoor clothes and no shoes). Information about weight will also be obtained by the RDs during the visits to the intervention group.

BMI is calculated as actual weight in kilograms divided by the square of height in meters.

As measurement of height is often not feasible in this chronic diseased, old and frail population, data on height will be retrieved from self-reported height.

#### Dietary intake (t = 0 and t = 12)

Dietary intake will be assessed by means of a 4-days dietary record. Participants will receive instructions from the research assistants on how to fill in the dietary record. They will receive the dietary records in advance of the visits at t = 0 and t = 12. At the visits the finalised records will be inspected and ambiguous entries clarified. The intake of energy and nutrients will be calculated by means of a computer program based on the Danish food composition table (available at: http://www.foodcomp.dk).

#### Hand grip strength (t = 0 and t = 12)

Hand grip strength (in kg) will be measured with a Jamar 5030J1 Hydraulic Hand Dynanometer. Participants will be seated with forearms rested on the arms of the chair. They are asked to perform three maximum force trials with their dominant hand and using the second handle position. The maximal grip score from the three values will be used.

#### Chair stand (t = 0 and t = 12)

To test the physical performance, the participants are asked to fold their arms across their chest and to stand up and sit dawn on a chair without pushing off with arms, as many times as possible during 30 seconds. The arms may be used for assistance or for safety if need [17].

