## Methods/design

### Design

This study is designed as a randomised controlled trial comparing discharge follow-up in patients' home by GP vs. discharge follow-up in patients' home by GP and RD. Patients are eligible for this study when they are 65+ years old and at nutritional risk according to the level 1 screen in NRS2002 [13].

The primary outcome parameter will be the prevalence of re-admissions in the intervention and control group. Secondary outcomes will be changes in body weight, muscle strength, quality of life, and rehabilitation capacity.

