### Feasibility of recruitment and sample size

An earlier study has shown that 50% of the elderly hospital population is at nutritional risk according to the level 1 screen [14]. For a clinically relevant difference of 10% in re-admissions and an expected drop-out rate of 12% (based on [12]), a statistical significant level of 0.05 and a power of 80%, two groups of 80 patients are calculated to be necessary.

A pilot study has shown that inclusion of up to 10 patients at nutritional risk per week is feasible. Taking in account an expected refusal rate of 30% at inclusion and loss to follow-up of 10% during the 12 weeks intervention, we aim to include two groups of 90, to be reached in approximately 6 months.

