### Statistical analysis

All statistical analysis will be performed using SPSS for Windows. Data will be entered in EXCEL and will subsequently be exported into SPSS software for analysis. Primary analysis for this study will be undertaken using intention to threat principles. 95% confidence intervals will be calculated for the differences in percentages, and medians. Independent samples t-test, Mann-Whitney U test and Chi-square test of association will be used as appropriate to compare groups at baseline. Ceiling and floor effect will be taken into account in the analysis of the questionnaires. In order to test the independent contribution of the intervention on the outcome variables, multivariate regression analysis will be used to adjust for the possible confounders. Specifically, the concordance between the GPs knowledge of the medical treatment and what the participant is actually taken plus the degree to which the GP have implemented the recommended follow-up as described in the hospital discharge letter, in respectively, the intervention and control group, will be used.

The analysis will be undertaken by the principal investigator blinded to the randomisation.

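### Chair stand: pushing off with the arms is ruled out, then arm assistance is allowed, with one count described and nothing that keeps the two modes apart

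*Protocol article*

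**What the plan says.** All references are to the protocol article.

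- **Chair stand, the instruction.** Participants are to "fold their arms across their chest and to stand up and sit dawn on a chair without pushing off with arms", and to do so "as many times as possible during 30 seconds". This is the only count described for the test.
- **Chair stand, the permission.** The next sentence reads "The arms may be used for assistance or for safety if need" and carries a literature citation for the test.
- **Outcome parameters.** Measurements are taken at home soon after discharge and again at 12 weeks. Research assistants collect the data unless stated otherwise, and the chair-stand section states nothing else.
- **Randomisation.** Allocation takes place just before the baseline assessment. The research assistants are listed among those not blinded. The principal investigator is re-blinded before analysis.
- **Design.** "Secondary outcomes will be changes in body weight, muscle strength, quality of life, and rehabilitation capacity". The chair stand is not named there, and the primary outcome is re-admission.
- **Statistical analysis.** "Ceiling and floor effect will be taken into account in the analysis of the questionnaires". This does not reach a performance test such as the chair stand.

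**The concern.** Rising without the arms and rising with them are different tasks. A count taken in one mode is not comparable with a count taken in the other, either between patients or between two visits of the same patient.

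The test is done twice, so the change from t = 0 to t = 12 is the natural quantity to compare. The first visit comes soon after discharge, when some patients may need their arms, and 12 weeks later they may not. Others may move the opposite way. If both modes feed one number, part of the measured change reflects the switch of mode rather than performance.

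Two features make this worse. The assessor decides when arms are needed, and the assessor knows the allocation at both visits. Re-blinding the analyst later cannot undo that judgement. And if arm use is not noted at the visit, the modes cannot be separated afterwards.

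**Working it through.** The plan gives no figure for this test: no expected count, standard deviation, target difference or rate of arm use. The only sample-size statement ("For a clinically relevant difference of 10% in re-admissions") concerns another outcome. The check is therefore a comparison of the text, followed by a logical test with assumed counts.

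**Step 1: the two sentences side by side.**

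| Sentence | Arms | What is counted |
|---|---|---|
| First | Folded, no push-off | Stands in 30 seconds |
| Second | Allowed for assistance or safety, when needed | Not stated |

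Use for safety could be reconciled with the first sentence, for example a hand put out to prevent a fall. Use for assistance cannot, because it is what the first sentence excludes.

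**Step 2: is the mode separated elsewhere?** The sections Design, Outcome parameters and Statistical analysis do not say whether an assisted stand is counted, scored zero or recorded apart. They do not require the same mode at both visits. The article does give scoring rules for other instruments: the best of three trials for grip strength, the conversion to a 0-100 score for DEMMI, and the component weights for the Functional Recovery Score.

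**Step 3: what each possible scoring rule does.** Assume a patient who needs the arms at t = 0 and makes 8 assisted stands, and who makes 6 unassisted stands at t = 12. These counts are illustrative and do not come from the documents. Change = count at t = 12 minus count at t = 0.

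| Scoring rule | t = 0 | t = 12 | Recorded change |
|---|---|---|---|
| (a) Assisted stands enter the single count | 8 | 6 | 6 - 8 = -2 |
| (b) Needing the arms scores 0 | 0 | 6 | 6 - 0 = +6 |
| (c) Assisted count kept as a separate test | 8 assisted | 6 unassisted | Not subtracted; reported as a move from assisted to unassisted |

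The patient has gained the ability to rise without arms. Rule (a) records a loss, (b) a gain, and (c) a change of category. With the visits exchanged (6 unassisted, then 8 assisted), rule (a) gives 8 - 6 = +2 for a patient who has lost that ability.

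**Step 4: what follows.** The misleading sign arises under rule (a) only. Rule (a) is the natural reading, since one count is described, but it is an inference. What the text does establish is that the same data can give -2 or +6 depending on a rule that the article does not state.

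**The case against.** The strongest reply has four parts.

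1. **A default with an exception.** The article says what participants are asked to do and then allows a fallback when needed, which is sensible in frail patients. It never says that assisted stands join the unassisted count. This stands: a reader might infer that improving patients will be scored as declining, but the documents do not support that as a description of the plan. It is the consequence of one possible scoring rule.

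2. **The rule may lie elsewhere.** The permitting sentence cites a source for the test, and the article condenses a fuller protocol. Neither is shown. This also stands, so the absence of a scoring rule is not by itself the point. The point is that two adjacent sentences give incompatible instructions on arm assistance.

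3. **No stated aim, no size.** A reader might infer that the intervention seeks to end arm use, so that the rule works against the dietician arm. The article states no such aim. It describes dietary counselling, leaves training out of the intervention, and speaks of mobility and function only in general terms. One could assume that the fall in arm use differs between arms by 5 to 15 percentage points and that arms add 2 to 4 stands. The distortion of the mean change would then be 0.05 x 2 = 0.1 to 0.15 x 4 = 0.6 stands. Both inputs are invented, the sum presupposes rule (a), and there is no standard deviation to judge the result against. It is not evidence of a material bias.

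4. **Modest status.** The primary outcome is register-based re-admission. Grip strength measures muscle strength directly, and DEMMI, the Mob-H scale and the Functional Recovery Score cover mobility and function. This limits the importance of the point but does not remove the conflict.

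**Conclusion.** The point holds in a limited form. The chair-stand section excludes arm push-off and then permits arm assistance, describes a single count, and does not tie the two visits to the same mode. Followed as written, it can mix two tasks between patients and over time, and the need for arms is judged by assessors who know the allocation.

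Whether the change score misleads depends on how assisted stands are scored. If they are pooled, individual changes can take the wrong sign in either direction (-2 or +2 in the illustration). If they score zero or are kept apart, that reversal does not arise. Neither the size nor the net direction of any effect on the comparison of arms can be derived from the documents.

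The primary analysis is not affected. The change is still worth making, because it is nearly free and unrecorded arm use cannot be recovered after data collection.

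**What to change.** - Reconcile the two sentences, so that it is clear whether a stand made with arm assistance belongs to the test.
- Record arm use (yes/no) at t = 0 and at t = 12.
- Analyse the unassisted count as the chair-stand outcome, with a stated score when the patient cannot rise without arms. Zero is the obvious choice; what matters is that the score is fixed in advance.
- Report arm-assisted counts separately and do not subtract across modes. The share of patients moving between assisted and unassisted in each arm can be reported alongside.

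The cost is one extra item on the test form and one or two sentences on scoring. The downside is more zero scores, which call for a rank-based or two-part summary instead of a plain comparison of means. Recording arm use does not blind the assessor, but it makes the decision visible so that the arms can be compared on it.

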#### Cognitive performance (t = 0 and t = 12)

The Mini Mental State Examination (MMSE) will be administered to assess cognitive status of the participants. The MMSE is a widely used and easily administered test of cognitive status. It consists of 11 tasks and is graded to assign old people a score in the range of 0 to 30.

Participants, who has difficulties with seeing, hearing or writing, will not be asked to complete the MMSE-test.

#### Activities of Daily Living (t = 0 and t = 12)

The ability to participate in activities of daily living (ADL) will be assessed using the validated de Morton Mobility Index (DEMMI) [18]. The DEMMI is a 15-item one-dimensional instrument that measures mobility across the spectrum from bed bound to independent mobility. The raw score total (0-19) must be converted to a DEMMI SCORE (0-100 where 100 is independent mobility).

#### Disability and tiredness in daily activities (t = 0 and t = 12)

Disability is measured by a validated scale (the Mob-H Scale) by asking questions about need of help in the following six activities: (1) transfer, (2) walk indoors, (3) get outdoors, (4) walk out of doors in nice weather, (5) walk out of doors in poor weather, and (6) manage stairs.

Tiredness in daily activities is measured by asking the participants if they feel tired after performing the same six activities [19].

#### Health-related quality of life (t = 0 and t = 12)

Quality of life is measured by questions from SF-36 regarding physical functioning; role-physical; bodily pain; general health; vitality; social functioning; role-emotional; mental health and health transition http://www.sf-36.org.

#### Rehabilitation capacity (t = 0 and t = 12)

The Functional Recovery Score (FRS) is used to assess restoration of function after discharge.

The eleven-item questionnaire is comprised of three main components: basic activities of daily living (BADL) assessed by four items, instrumental activities of daily living (IADL) assessed by six items, and mobility assessed by one item. Basic activities of daily living comprise 44 percent of the score; instrumental activities of daily living comprise 23 percent, and mobility comprises 33 percent. Complete independence in basic and instrumental activities of daily living and mobility results in a score of 100 percent [20]. Participants will receive instructions from the research assistants on how to fill in the questionnaire. They will receive the questionnaire in advance of the visits at t = 0 and t = 12. At the visits the finalised questionnaire will be inspected and ambiguous entries clarified.

### Organisation

The primary investigator is responsible for the informed consent procedure, final participants' selection, measurements, analysis and reports. The primary investigator will be assisted by two research assistants and two RDs. Data flow will be controlled by the primary investigator. Data-entry and control will be conducted by the research assistants under supervision of the investigator. The primary investigator is responsible for the data cleaning and analysis.

### Statistical analysis

All statistical analysis will be performed using SPSS for Windows. Data will be entered in EXCEL and will subsequently be exported into SPSS software for analysis. Primary analysis for this study will be undertaken using intention to threat principles. 95% confidence intervals will be calculated for the differences in percentages, and medians. Independent samples t-test, Mann-Whitney U test and Chi-square test of association will be used as appropriate to compare groups at baseline. Ceiling and floor effect will be taken into account in the analysis of the questionnaires. In order to test the independent contribution of the intervention on the outcome variables, multivariate regression analysis will be used to adjust for the possible confounders. Specifically, the concordance between the GPs knowledge of the medical treatment and what the participant is actually taken plus the degree to which the GP have implemented the recommended follow-up as described in the hospital discharge letter, in respectively, the intervention and control group, will be used.

The analysis will be undertaken by the principal investigator blinded to the randomisation.

### Ethics

The protocol has been send to the Danish Ethical Board which has concluded that approval is not needed and that the project can be carried on as described.

## Discussion

This project is the first to combine individualised nutritional intervention with intervention from GPs.

We have chosen not to use strict exclusion criteria, but to include all eligible patients even though they are suffering from a variety of (chronic) diseases. Their homogeneity stems from their age (65+ years old), nutritional risk and background of disease (non-surgical). If the results of a broad study like this one are positive, it justifies wide implementation, because the included group is representative for a mixed elderly population; in contrast, selection of a more specific group would make the intervention less applicable to other patients group.

In Denmark it is recommended that the nutritional management of (geriatric) patients involves the provision of high energy, high protein diets and individualised nutritional therapy [15], however the evidence for this, is limited. A review of the literature highlighted that most nutrition support provided for geriatric patients is based on the provision of a standard volume of commercial oral nutritional supplements rather than individualised therapy [21]. Specifically, former nutritional intervention studies among geriatric medical patients after discharge has all used commercial oral nutritional supplements [5-8].

A comprehensive approach to nutritional therapy combining individual education, motivation and counselling, dietary modification and supplementation offered by a RD, differs from previous work, however was deemed necessary given the limited evidence that commercial oral supplements alone can improve outcomes in this frail group.

Strength training is an effective intervention for improving physical functioning in older people [22]. In Denmark it is part of the legislation to offer some patients rehabilitation in the form of physiotherapy. In this study, it was therefore decided not to include training as a specific part of the comprehensive intervention, but instead register if there is a difference in the prevalence between the two groups.

Most of the former discharge studies may have had an intervention time that was too short to have a realistic chance of detecting differences in morbidity, functional status or quality of life. According to a recent Cochrane Review future trials need to have sufficient statistical power and length of follow-up to be able to detect any beneficial effects [23]. The follow-up period of 12 weeks is therefore chosen because this seems a reasonable time to achieve benefits of nutritional intervention in older people at nutritional risk. Further, in a former study of discharge follow-up in patients home by GPs, there was seen a significant different in the number of re-admissions after 12 weeks [12].

